## Abstract

**Introduction::**

Low back pain (LBP) is ranked as one of the most prevalent health conditions. It is likely that some inflammatory mediators could be associated with pain and disability in these patients. Photobiomodulation therapy (PBMT) is a non-pharmacological therapy often used in patients with LBP and one of the possible mechanisms of action of therapy is modulate inflammatory mediators. However, to date there are no studies that evaluated the effects of PBMT on the levels of inflammatory mediators in patients with LBP. The aim of this study is to evaluate the acute effects of PBMT on systemic levels of inflammatory mediators and pain intensity in patients with chronic non-specific low back pain.

**Methods and analysis::**

This is a prospectively registered, two-arm randomized placebo-controlled trial with blinded patients, assessors and therapists. Eighteen patients with chronic non-specific LBP will be randomized into 2 groups: placebo or active PBMT. The treatment will be provided in a single session. The primary outcome will be levels of prostaglandin E_2_ (PGE_2_). The secondary outcomes will be levels of necrosis factor alpha (TNF-α), interleukin 6 (IL-6) and pain intensity. Biochemical and clinical outcomes will be measured at baseline and 15 minutes after the single treatment session.

**Discussion::**

Despite PBMT be used in musculoskeletal disorders such as LBP, to the best of our knowledge this is the first study that will investigate a possible biological mechanism behind the positive clinical effects of PBMT on non-specific chronic low back pain.

**Ethics and dissemination::**

The study was approved by the Regional Research Ethics Committee. The results will be disseminated through publication in peer-reviewed international journal and conferences.

**Trial registration number::**

NCT03859505.

## Introduction

1

Non-specific low back pain is a complex and extremely frequent condition^[1]^ strongly associated with high levels of disability.^[2]^ Some aspects can be associated with low back pain, and the identification of these aspects is helpful in both prevention and management of this condition.^[3]^ One of these aspects is the possible association between inflammatory mediators and low back pain, since the increased of pro inflammatory cytokines levels is often observed in painful conditions.^[4,5]^

Evidences have demonstrated increase of pro inflammatory cytokines levels in patients with low back pain. Wang et al^[6]^ demonstrated increase of plasmatic levels of necrosis factor alpha (TNF-α) in patients with chronic low back pain when compared to healthy individuals, for example. However, no significant correlation of TNF-α levels to pain intensity or disability were identified. Moreover, it was observed that there is an increase of TNF-α ^[7,8]^ and interleukin (IL) 6 levels in patients with acute low back pain.^[8]^ Thus, the presence of some inflammatory mediators might be associated with pain and disability in patients with low back pain, since pro inflammatory cytokines such as IL-6, TNF-α and IL-1 contribute to the activation of nociceptors that generate potential of action and pain hyper sensibility.^[4,5]^

Several nonpharmacologic and noninvasive management options are available for patients with low back pain (e.g., exercises, electrophysical agents and manual therapy).^[9]^ However, the mechanisms of action of available therapies to reduce pain and disability in these patients still remain uncertain. According to the abovementioned studies,^[6–8]^ the modulation of inflammatory mediators levels could be considered a possible strategy in the low back pain management and thus, the use of photobiomodulation therapy (PBMT) could be interesting in this case.

PBMT is a non-pharmacological and non-thermal intervention that consists in applying a non-ionized form of light, which includes LASER (light amplification by stimulated emission of radiation) and LED (light-emitting diodes) from visible to infrared spectrum.^[10]^ PBMT is often used in the treatment of musculoskeletal disorders such as low back pain;^[11,12]^ however, the exact mechanism of action through PBMT decreases pain intensity and disability in these patients is still unknown. Evidences suggest that PBMT is effective in modulate inflammatory mediators such as TNF-α, IL-1β, IL-6, IL-10 and prostaglandin E_2_ (PGE_2_), both in experimental and clinical studies,^[13–18]^ contributing to pain relief^[18,19]^ and tissue repair.^[20,21]^ The biological responses of PBMT on these inflammatory mediators may be targeted as possible mechanism of action for its beneficial clinical effects.

However, currently there are no studies about the effects of PBMT on inflammatory mediators in patients with non-specific low back pain, investigating whether this could be a possible mechanism of action. Therefore, the aim of this study is to evaluate the acute effects of PBMT on systemic levels of inflammatory mediators (TNF-α, IL-6 and PGE_2_) and pain intensity in patients with chronic non-specific low back pain.

## Methods and analysis

2

### Design

2.1

A two-arm, parallel randomized, triple-blinded (patients, therapists and outcome assessors), placebo-controlled trial will be performed. The protocol of this study has been prospectively registered on Clinicaltrials.gov (NCT03859505). The study will be conducted at Department of Global Public Health and Primary Care, University of Bergen, Norway.

### Ethical aspects

2.2

The present study will follow the ethical guidelines and was approved by the Regional Research Ethics Committee (Protocol No. 2018/1361/REK nord). Patients will be informed about all study procedures and asked to sign the Informed Consent Form prior to their enrollment in the study. Research personnel will take all appropriate and customary steps to ensure that data remain secure and that patient privacy and confidentiality will be maintained.

### Characterization of sample

2.3

Since no studies assessing the effects of PBMT on inflammatory mediators in patients with non-specific low back pain are available, the number of patients per group in the present study was calculated based on a pilot study. This pilot study was recently conducted by our research group with 3 patients per group in order to estimate the sample size. A β value of 20% and an α of 5% were used to calculate the sample size. The pilot study showed that applying PBMT in patients with non-specific low back pain resulted in levels of PGE_2_ (primary outcome of the present study) of 1.05 pg/μl (0.42 standard deviation), whereas applying the placebo in patients with non-specific low back pain resulted in levels of PGE_2_ of 1.52 pg/μl (0.39 standard deviation). We used the Researcher's Toolkit to calculate the sample size (https://www.dssresearch.com/resources/calculators/sample-size-calculator-average). Based on the aforementioned parameters used to calculate the sample, we found a sample of 9 patients per group, for a total of 18 patients. Since the phototherapy device used in the study causes no harmful thermal effects,^[22]^ patients of different skin colors will be recruited. The patients will be recruited through primary care doctors and physiotherapists.

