## Discussion

3

Despite PBMT be used in musculoskeletal disorders such as low back pain, to the best of our knowledge this is the first study that will investigate a possible biological mechanism behind the positive clinical effects of PBMT on non-specific chronic low back pain. We strongly believe that this investigation can be helpful in the management of this condition.

Non-specific low back pain is a complex health condition and several treatment options may be used for symptoms relief.^[29]^ Over the years, it has been believed that some subgroups of this population can benefit from specific treatments, responding favorably to specific therapies.^[30,31]^ In this way, knowing the mechanism of action of available therapies becomes an important aspect in this process.

PBMT triggers positive effects acting in different ways, including increase of microcirculation,^[32]^ cytochrome c oxidase modulation and ATP synthesis,^[33]^ besides modulating some inflammatory biomarkers.^[17,18]^ Thus, if PBMT is able to modulate inflammatory mediators in non-specific low back pain, patients with increased levels of these mediators might be more responsive and consequently benefit more with the use of therapy.

It is important to highlight that the present study is innovative and present high methodological quality (i.e., is a randomized controlled trial, triple blinded and prospectively registered). The sample size was calculated to provide the appropriate statistical power to detect precise differences for the primary outcomes of the study; however, the sample size has not powered enough to be correlated with the secondary outcome (pain intensity). One of the limitations of the study is that although the PBMT parameters were based on previous studies, there was no optimization and only one dose will be tested.

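### The sample size treats estimates from a pilot of 3 patients per group as known, so the Discussion's unqualified claim of appropriate power for PGE2 is not supported

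*Protocol article*

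**What the plan says.** Section 2.3 (Characterization of sample) explains that no earlier data on this therapy and inflammatory mediators existed in this population, and that the size therefore rests on the group's own pilot: "This pilot study was recently conducted by our research group with 3 patients per group in order to estimate the sample size". The error rates are given as: "A β value of 20% and an α of 5% were used to calculate the sample size". The pilot PGE2 level under active treatment is reported as "primary outcome of the present study) of 1.05 pg/μl (0.42 standard deviation") and under placebo as "of 1.52 pg/μl (0.39 standard deviation"). From these inputs, "we found a sample of 9 patients per group, for a total of 18 patients". The section gives no interval for the difference, no margin for uncertainty in the SD, and does not say whether the 5% is one- or two-sided.

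Section 2.9 (Statistical analysis) plans a two-way repeated-measures ANOVA of time and group for parametric data, using the baseline and 15-minute samples described in section 2.8.

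Section 3 (Discussion) states: "The sample size was calculated to provide the appropriate statistical power to detect precise differences for the primary outcomes of the study". The only reservation about power there concerns pain intensity, a secondary outcome.

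**The concern.** A sample size calculation delivers its nominal power only if the difference and SD put into it are right. Here both come from six patients and enter without any allowance for error. Section 3 nevertheless presents the power for PGE2 as settled. If the true SD is larger or the true difference smaller than the pilot's, both of which the pilot leaves open, power at 9 per group is well below 80%.

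What is at stake is interpretation. The trial is presented as the first to examine a biological mechanism for this therapy in chronic low back pain. A reader who has been told that power is appropriate may give a non-significant PGE2 result more weight than the design can bear.

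**Working it through.** **Inputs (section 2.3).** PGE2 means 1.05 and 1.52 pg/μl; SDs 0.42 and 0.39; 3 per group in the pilot; α 5%, β 20%; 9 per group in the trial.

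**1. Planning values.** Difference = 1.52 − 1.05 = 0.47. Pooled SD = √[(0.42² + 0.39²)/2] = √0.16425 = 0.405. Standardised difference d = 0.47/0.405 = 1.16.

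**2. The plan's own figure.** Normal approximation for two independent means, n per group = 2[(z_α + z_β) × SD/difference]².
- One-sided 5%: 2[(1.645 + 0.842) × 0.405/0.47]² = 9.19, which matches 9 if rounded to the nearest whole number (10 if rounded up).
- Two-sided 5%: the same with 1.960 gives 11.67, so 12 per group; the t-test version gives 12.7, so 13.

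So 9 per group is reproduced only by a one-sided calculation, and the sidedness is not stated.

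**3. Precision of the pilot difference.** SE = √(0.42²/3 + 0.39²/3) = √0.1095 = 0.331. With t(4) = 2.776, the 95% CI is 0.47 ± 0.92, that is -0.45 to 1.39. This interval is derived here and assumes two independent groups of 3; the Welch version is practically identical.

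**4. Precision of the pilot SD.** 95% limits = √(4 × 0.16425/χ²), with χ²(4) quantiles 11.143 and 0.484: √(0.657/11.143) = 0.24 and √(0.657/0.484) = 1.16. The range is nearly five-fold.

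**5. Power at 9 per group, comparison of levels.** Noncentral t with 16 df and noncentrality (difference/SD) × √(9/2).

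| Difference | SD | Two-sided 5% | One-sided 5% |
|---|---|---|---|
| 0.47 | 0.24 | 97% | 99% |
| 0.47 | 0.405 | 64% | 76% |
| 0.47 | 0.60 | 35% | 48% |
| 0.47 | 1.16 | 13% | 20% |
| 0.30 | 0.405 | 31% | 44% |
| 0.20 | 0.405 | 17% | 26% |

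The d detectable with 80% power, two-sided, is 1.41, or 1.41 × 0.405 = 0.57 pg/μl at the pilot SD.

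**6. Power at 9 per group, time-by-group analysis.** With two time points, the interaction test is equivalent to comparing change scores. Assuming the same SD at both times, the SD of change = SD × √[2(1 − r)], where r is the baseline to follow-up correlation. The document gives no r, so the values below are assumptions. Difference 0.47, SD 0.405, two-sided 5%:

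| r | SD of change | Power | d detectable with 80% power (in SDs of levels) |
|---|---|---|---|
| 0 | 0.573 | 37% | 1.99 |
| 0.5 | 0.405 | 64% | 1.41 |
| 0.7 | 0.314 | 85% | 1.09 |
| 0.8 | 0.256 | 95% | 0.89 |

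A favourable r does not remove the SD problem. At r = 0.7, power for 0.47 is 52% if the SD of levels is 0.60 and 18% if it is 1.16.

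**7. Would a two-sided size cure it?** With 13 per group, power for levels is 81% if the pilot values are exact. Over the same SD interval (24 df, noncentrality (0.47/SD) × √(13/2)) it still runs from over 99% to 17%. The imprecision is therefore a separate matter from how 9 was obtained.

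**The case against.** The best defence has four parts.

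*The pilot is openly disclosed and nothing better existed.* Section 2.3 gives its size, means and SDs, so a reader can see the imprecision. This stands, and running a pilot or choosing 18 patients is not at fault. But scarce data are a reason to qualify a power statement, and section 3 does not qualify it for PGE2.

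*The pilot was meant to estimate, not to test.* This also stands. A reader might infer from an interval that includes zero that the planning was invalid. The document does not support that: such an interval is expected with 3 per group, and section 2.3 says the pilot was run to obtain planning values. The interval matters here only as a measure of how loosely the values are known.

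*The powers for levels do not describe the planned analysis.* Correct, and this limits the point. A reader might infer that the design can detect only d of about 1.4 or more. That holds for a comparison of levels, or for change scores if r is about 0.5. At r = 0.8 the figure is 0.89, and power at the pilot values is 95%. Since r is not given, the document supports neither a fixed detectable effect nor the claim of appropriate power.

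*No one has said a null result will count against the mechanism.* True. Section 3 speaks conditionally about what follows if the therapy modulates the mediators. The misreading is a risk that the unqualified claim creates, not something the document commits to.

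A power table could be left to a fuller document, and its absence alone would be no fault. The power claim, however, is in the text shown.

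**Conclusion.** The point holds as one about an unqualified claim. Section 3 asserts appropriate power for PGE2, but that rests on a difference and SD estimated from six patients and treated as exact. For a two-sided comparison of levels, power at the pilot values is 64% (76% one-sided), with a range of 97% to 13% over the 95% interval for the SD. For the planned time-by-group analysis it runs from 37% at r = 0 to 95% at r = 0.8 at the pilot values, with r unknown.

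These figures assume independent groups, approximately normal data, the quoted SDs as between-patient SDs of PGE2 levels, equal SDs at both times for the change-score results, and no dropout. They do not show that the trial is underpowered for its planned analysis; they show that the document gives no basis for saying that it is adequately powered.

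**What to change.** Keep 18 patients and change the wording in two places.

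- **Section 3:** delete the claim of appropriate power to detect precise differences in the primary outcome. Say instead that the size rests on a pilot of 3 per group and that power is uncertain.
- **Section 2.3:** state whether the 5% is one- or two-sided. Give power over a range of SDs (for example 0.24 to 1.16), differences (for example 0.20 to 0.57 pg/μl) and assumed r. Label any detectable effect as conditional: d of about 1.4 applies to levels, or to change scores at r = 0.5.
- **Interpretation:** state in advance that the PGE2 result will be read from the 95% CI of the between-group difference, so that non-significance is not taken as absence of effect.

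The cost is a few sentences and a small table, with no extra patients. The downside is that the stated power becomes less favourable.

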### Statistical analysis

2.9

The statistical analysis will be conducted following the principles of intention-to-treat analysis.^[28]^ The findings will be tested for their normality using the Shapiro-Wilk test. Parametric data will be expressed as mean and standard deviation and non-parametric data as median and respective upper and lower limits. Parametric data will be analyzed by two-way repeated measures analysis of variance (ANOVA, time vs experimental group) with post-hoc Bonferroni correction. Non-parametric data will be analyzed using the Friedman test and, secondarily, the Wilcoxon signed-rank test.

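### With the stated pilot figures, 9 patients per group gives about 64% power, not 80%, for a two-sided 5% comparison of group means; the 9 fits an undeclared one-sided formula

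*Protocol article*

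**What the plan says.** Section 2.3 (Characterization of sample) bases the sample size on a pilot run "with 3 patients per group in order to estimate the sample size". It reports post-intervention PGE2, the primary outcome, as a mean of 1.05 pg/μl (SD 0.42) with active treatment and 1.52 pg/μl (SD 0.39) with placebo. The error rates are given in one sentence: "A β value of 20% and an α of 5% were used to calculate the sample size". An online calculator for averages was used, and the result is "we found a sample of 9 patients per group, for a total of 18 patients". The section does not say whether α is one-sided or two-sided.

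Section 2.9 (Statistical analysis) plans, for parametric data, a "two-way repeated measures analysis of variance (ANOVA, time vs experimental group") with Bonferroni post-hoc comparisons. No directional hypothesis appears there or elsewhere.

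The Discussion (section 3) returns to the subject: "The sample size was calculated to provide the appropriate statistical power to detect precise differences for the primary outcomes of the study".

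**The concern.** Section 2.3 prints both the inputs and the result, so the calculation can be repeated. Under the usual two-sided reading of α 5%, the inputs do not lead to 9 per group. That reading is also the one that matches the planned analysis, because an ANOVA F-test does not distinguish direction.

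At stake is the stated type II error for the primary outcome. If β is well above 20% for the comparison used to size the trial, then section 2.3 and the Discussion both credit the design with more power than their own figures support.

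**Working it through.** **Inputs, all from section 2.3.** Means 1.52 and 1.05, so the difference is 1.52 − 1.05 = 0.47 pg/μl. SDs 0.42 and 0.39. α 5%, β 20%, equal groups.

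0.42² + 0.39² = 0.1764 + 0.1521 = 0.3285. The root-mean-square SD is √(0.3285/2) = 0.405. The standardised difference is 0.47/0.405 = 1.16.

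**Normal formula.** n per group = (z_α + z_β)² × (SD₁² + SD₂²) / difference², with 0.47² = 0.2209.

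*The plan's own figure, one-sided.* (1.645 + 0.842)² ≈ 6.18, and 6.18 × 0.3285/0.2209 = 9.19. This lies next to the stated 9, but rounds up to 10.

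*Two-sided.* (1.960 + 0.842)² ≈ 7.85, and 7.85 × 0.3285/0.2209 = 11.67, so 12 per group (24 in total).

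**Power for a standardised difference of 1.16** (t-test figures from the noncentral t distribution with 2n − 2 degrees of freedom):

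| Test | n per group | Normal | t-test |
|---|---|---|---|
| Two-sided 5% | 9 | 69.2% | 63.7% |
| Two-sided 5% | 12 | 81.1% | 77.5% |
| Two-sided 5% | 13 | 84.1% | 81.0% |
| One-sided 5% | 9 | 79.3% | 76.1% |
| One-sided 5% | 10 | 82.9% | 80.2% |

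The two-sided t-test therefore needs 13 per group (26 in total). At 9 per group none of the four figures reaches 80%.

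**Detectable difference.** With 9 per group and a two-sided 5% t-test, 80% power requires a standardised difference of 1.41. That is 1.41 × 0.405 = 0.57 pg/μl, against the assumed 0.47.

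**Other ways of combining the SDs.** With 0.39 in both groups, the two-sided normal formula gives 10.8, so 11; the one-sided formula gives 8.51, so 9. With 0.42 in both groups the results are 12.5 two-sided and 9.9 one-sided. No choice of the stated SDs yields 9 from a two-sided test.

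**The planned group-by-time test.** With two time points, this test is equivalent to comparing mean changes between groups. The SD of change is SD × √(2(1 − r)), where r is the baseline-to-post correlation. The article gives no r. Assuming equal SDs of 0.405 at both times and a between-group difference in change of 0.47, two-sided power at 9 per group is:

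| Assumed r | Power |
|---|---|
| 0.3 | 50% |
| 0.5 | 64% |
| 0.65 | 79% |
| 0.7 | 85% |
| 0.8 | 95% |

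**The case against.** **The article never says two-sided.** True. The 9 is close to a one-sided calculation with nominal power of 79.3%, and the shortfall from rounding 9.19 down is 0.7 of a percentage point. On this view the defect is undeclared sidedness, not failed arithmetic. That description is fair, but it does not rescue the figure: no one-sided hypothesis is declared, the ANOVA in section 2.9 is non-directional, and a one-sided size does not match it.

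**The route to 9 is not certain.** A reader might infer that 9 can come only from a one-sided formula rounded down. The article does not support that. It does not say how the two SDs were combined, and with 0.39 in both groups the one-sided formula gives 8.51, which rounds up to 9. What the online calculator did cannot be seen. What stands is that either route is one-sided.

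**The 64% is not the power of the planned analysis.** This stands. A reader might infer that the trial as designed has more than a one-in-three chance of missing the assumed effect. That holds for a post-treatment two-group t-test. Samples taken before and shortly after one session could correlate highly, and at a correlation of 0.7 the group-by-time test would exceed 80%. But the article states no correlation, sizes the trial on two group levels, and at a correlation of 0.3 power would be lower still, so the point does not support the stated β.

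**The inputs are themselves uncertain.** This also stands. With 3 pilot patients per group (4 degrees of freedom), a 95% interval for the SD runs from about 0.24 to 1.16. Two-sided t-test power at 9 per group for a 0.47 difference then runs from 97% down to 13%. So 64% is what the stated inputs imply, not a precise forecast.

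**How a null result would be read.** The article does not say, so no claim about a misread null result is made here.

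**Conclusion.** The point holds as a mismatch between the stated inputs, the stated error rates and the stated size. For a two-sided 5% comparison of post-treatment means, β at 9 per group is about 36% by the t-test (100 − 64) or 31% by the normal approximation (100 − 69), not 20%. The size needed for 80% power is 13 or 12 per group respectively.

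The conclusion rests on the two pilot means and SDs as printed, equal groups, and a two-sided test. The last is taken from the non-directional ANOVA and the absence of any declared one-sided hypothesis, not from an explicit statement. The conclusion does not extend to the power of the group-by-time test, which cannot be fixed without a baseline-to-post correlation. The Discussion's power sentence is unsupported as it stands.

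**What to change.** In section 2.3:

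- State whether α is one-sided or two-sided, consistently with section 2.9.
- Restate the result: for a two-sided 5% t-test of post-treatment PGE2, 9 per group gives about 64% power for a difference of 0.47 pg/μl, and about 0.57 pg/μl is detectable with 80% power. Both figures use an SD of 0.405, which comes from 3 pilot patients per group.
- Add that the power of the planned group-by-time test depends on the baseline-to-post correlation. Assuming equal SDs and a 0.47 difference in change, it is about 50% at a correlation of 0.3, 64% at 0.5 and 85% at 0.7.

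In the Discussion, qualify the power sentence to agree with this.

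The change is wording only and needs no extra patients. Its cost is a less favourable stated figure. If the sponsor prefers to keep 80% power for the two-sided post-treatment t-test, the matching size is 13 per group, 26 in total, which is 8 more than planned.
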